## Methods and Analysis

### Study Setting and Organization

The trial is a single center study and will be executed at the Ghent University Hospital (Belgium). All participants will complete the same protocol on both test days, however consuming a different type of capsules in a randomized order: high-flavanol cocoa extract or placebo. The flavanols used in this trial were extracted from the cocoa bean. A wash-out period of minimal 3 days and maximal 2 weeks is provided. The first measurement was conducted on October 5th, 2018 and since the COVID-19 pandemic forced to cancel all measurements for about 6 months, the end date of the study was postponed and is estimated in June 2021.

### Participants

#### Eligibility Criteria

All subjects are divided in four groups: (i) patients with T2DM with arterial hypertension (with BB, *n* = 5/ACEi, *n* = 5/ARB, *n* = 5) (*n* = 15), (ii) patients with T2DM without arterial hypertension (*n* = 10), (iii) non-diabetic patients with essential arterial hypertension (BB, *n* = 10/ACEi, *n* = 10/ARB, *n* = 10) (*n* = 30), and (iv) healthy participants (control group; *n* = 20).

Inclusion and exclusion criteria are summarized in Table 2.

**Table 2 T2:** In- and exclusion criteria for participants in this study.

**Inclusion criteria**
Male and female; age: 18–85 years; BMI: 20–40 kg/m^2^
(i) Patients with T2DM without arterial hypertension: at least 5 years T2DM [HbA1c ≥6.5%, glucose (fasting) ≥126 mg/dl, glucose (not fasting): ≥200 mg/dl, defined by the American Diabetes Association (ADA) (55)]
(ii) Patients with T2DM with arterial hypertension: at least 5 years T2DM [HbA1c ≥6.5%, glucose (fasting) ≥126 mg/dl, glucose (not fasting): ≥200 mg/dl, defined by the American Diabetes Association (ADA) (55)] AND at least 1 year arterial hypertension taking BB, ACEi or ARB (optionally combined with diuretics)
(iii) Patients with essential arterial hypertension: at least 1 year arterial hypertension taking BB, ACEi or ARB (optionally combined with diuretics), matched by age, sex, and BMI with subjects with T2DM
(iv) Healthy controls: taking no medication except for contraceptive drugs, matched by age, sex, and BMI with subjects with T2DM
**Exclusion criteria**
Smoking habits: current smoking; smoking history of more than 30 years or pack years are higher than years of smoking cessation
Alcohol consumption: more than 10 units per week
Additional systemic disorders: chronic inflammatory disease, active cancer
Microvascular complications: retinopathy, nephropathy, peripheral sensory(motor), or autonomic neuropathy
Macrovascular complications: cardiovascular and respiratory diseases: heart failure NYHA class 3 and 4, uncontrolled arrhythmias or angora, documented peripheral arterial disease or experienced heart attack, active or chronic recurrent vasculitis, severe to very severe chronic pulmonary diseases (GOLD stage III and IV)
Neurological diseases: cerebrovascular accident, transient ischemic attack, reversible ischemic neurological deficit or stenosis >50% by doppler
Other: important (and relevant) musculoskeletal disorders; factors that impede the execution of the dynamic handgrip exercise test; pregnancy; known cognitive impairment (such as dementia, intellectual disability), language barriers
Medication: medication directly influencing endothelial function except for insulin or antihypertensive drugs; nitric oxide-containing medication; phosphodiesterase type 5-inhibitors

*T2DM, type 2 diabetes mellitus; BMI, body mass index; BB, beta blocker; ACEi, angiotensin converting enzyme inhibitor; ARB, angiotensin receptor blocker*.

#### Recruitment and Screening

Subjects are recruited by endocrinologists and other medical specialists, general practitioners, dieticians and investigator's acquaintances. Flyers are distributed in the Ghent University Hospital and by pharmacists and physiotherapists. In addition, the essential information for possible participants of our study is disseminated on media and social media.

#### Patient and Public Involvement

No patient or patient advisor was/is involved with study design, recruitment or conduct.

### Intervention

#### Study Protocol

As depicted in Figure 1, patients will arrive at the lab (Ghent University Hospital) at 8 o'clock after an overnight fast of minimal 8 h. Blood samples will be collected and participants will be evaluated for body composition [weight, height, skinfolds, and fat% (bio-electrical impedance analyzer)] and BP, followed by a standardized breakfast with negligible flavonoid and nitrate/nitrite amounts, in accordance to guidelines of a dietician (Table 3), and consumed within 15 min. Participants have to choose 1 formula of breakfast which will be consumed at both visits. After 15 min rest period, a baseline Flow-Mediated Dilation (FMD) measurement will be performed, followed by the ingestion of CF-enriched capsules (2.5 g of cocoa extract which contains 790 mg flavanols of which 150 mg epicatechin, *Naturex*^©^, *France*) or placebo (maltodextrin and an equivalent dose of theobromine and caffeine compared to the CF-enriched capsules) (Table 4). The dose of CF given in this study is based on the research of Balzer et al. (41) who investigated the effect of different doses of CF (high dose = 963 mg CF of which 203 mg epicatechin, medium dose = 371 mg CF of which 78.9 mg epicatechin, and low dose (control) = 75 mg CF of which 16.8 mg epicatechin), closely matched for theobromine and caffeine, on FMD in 10 patients with T2DM. The equilibration of theobromine and caffeine, both vasoactive compounds of cocoa (38, 56, 57), in the different interventions is a very important quality of this study and will ensure to test isolated vascular effects of CF.

**Figure 1 F1:**
[figure not shown]
Flowchart. FMD, flow-mediated dilation test; capillary blood, finger prick to measure capillary glycaemia (only patients with T2DM).

**Table 3 T3:** Standardized breakfast formulas.

**Breakfast formulas**	**Composition**	**Ingredients**
Formula 1	Energy: 418 Kcal Proteins: 21.7 g (21%) Carbohydrates: 61.4 g (59%) Fat: 8.8 g (20%)	60 g cereals (Special K, Kellogg's) 200 g semi-skimmed milk 125 g semi-skimmed cottage cheese
Formula 2	Energy: 386 Kcal Proteins: 19.3 g (21%) Carbohydrates: 49.5 g (53%) Fat: 10.8 g (26%)	90 g light brown bread 15 g butter (Halvarine, Blue Band) 17 g cream cheese (La vache qui rit) 15 g jam (reduced sugars) 125 g low-fat yogurt
Formula 3	Energy: 499 Kcal Proteins: 23.3 g (19%) Carbohydrates: 53.9 g (44%) Fat: 20.0 g (37%)	90 g light brown bread 200 g semi-skimmed milk 15 g butter (Halvarine, Blue Band) 15 g jam (reduced sugars) 30 g cheese (Gouda, Hollandic)
Formula 4	Energy: 501 Kcal Proteins: 22.4 g (18%) Carbohydrates: 58.6 g (48%) Fat: 17.6 g (33%)	90 g light brown bread 15 g butter (Halvarine, Blue Band) 25 g gingerbread (reduced sugars) 30 g cheese (Gouda, Hollandic) 125 g low-fat yogurt

**Table 4 T4:** Nutrient content of the capsules.

**Nutrient content**	**8 CF-enriched capsules**	**6 capsules with placebo**
Total cocoa extract (g)	2.5	0
Total flavanols (mg)	794	0
Epicatechin (mg)	149	0
Catechin (mg)	30	0
Caffeine (mg)	23	24
Theobromine (mg)	179	180
Maltodextrin (mg)	928	1.956

*Amount is presented for total amount taken and not for each capsule. CF, Cocoa flavanols*.

The investigator will ensure all capsules are taken in properly. After ingestion, the participants will remain seated for 70 min. Thereafter, blood samples will be collected and a second BP and FMD assessment followed by a dynamic handgrip exercise (dHGE) test with simultaneous near-infrared-spectroscopy (NIRS) monitoring and blood flow measurements will be executed. Venous blood samples will be drawn before and after the dHGE test.

All measurements post intake will be performed within 2 h as highest circulating concentrations of flavanols are found between 90 and 120 min after consumption (58, 59).

Participants will fill in questionnaires (once) to evaluate factors which may impact vascular reactivity [i.e., daily physical activity [International Physical Activity Questionnaire—long version (60)], flavanols-intake [a self-designed questionnaire about the frequency of flavanol-enriched food intake (16, 17, 61)], sleep behavior (Epworth Sleepiness Scale, STOP-BANG), and autonomic function (Autonomic Symptom Profile-COMPASS). We will also assess quality of life and general health status (36-Item Short Form Health Survey, World Health Organization Quality of Life questionnaire-BREF, and only for patients with T2DM Diabetes Quality Of Life questionnaire). In addition to the questionnaires, each participant's physical activity levels (62) and glycemic excursions and variability (63) will be objectively measured during 1 usual week using accelerometry and a Continuous Glucose Monitoring System, respectively.

#### Guidelines for Participants

Subjects will be asked not to participate in other trials from 3 weeks before start of this study to 1 week after the second study day. Supplement or vitamin consumption that could interfere with the mechanisms of action of flavanols have to be suspended for at least 4 weeks prior start of the study. In addition, to minimize flavanol intake before each study day, participants will be asked to follow guidelines (16, 17, 61):

➣ 3 days before each study day, participants will be asked to drink maximal two cups of tea per day, to avoid red wine or cider, to refrain from eating chocolate (in any form), beans, and rhubarb and to consume maximal two small portions of fruits (piece, juice, or jam) or one portion in combination with 10 g nuts.➣ Twenty-four hours before each study day, participants will be asked to refrain from vigorous physical activity (apart from daily movements as climbing stairs, biking to the train station, walking to the car etc.), alcohol or caffeine containing drinks (e.g., coffee, cola, and tea). They have to consume the same meal the evening before both study days.➣ Eight hours before the actual start of the study, participants will be asked to fasten (no food or drink intake, apart a small amount of water) and, importantly, to take in their medication as usual (identical dose as prescribed by their physician). Antihypertensive medication need to be taken in exactly 2 h before actual start of the study. Antidiabetics must be taken in at home or at the lab during breakfast depending on type of the drug. Metformin, SGLT-2 inhibitors, and GLP-1 analoga may be taken in at home or at the lab and all sulfonylurea drugs must be taken in at the lab during breakfast. For insulin, the long-acting insulin must be taken in at home and the short-acting insulin must be taken in at the lab during breakfast.

#### Blinding and Randomization

In this cross-over study, every participant will receive CF-enriched and placebo capsules. Randomization of capsules will be done by sealed envelopes and type of capsules will be indicated by number 1 or number 2. Each participant may choose 1 envelope at the first study day. Both types of capsules have an identical look and taste. Hence, participants will be blinded to their group allocation. Furthermore, since type of capsules will be identified by numbers, outcome assessors and personnel involved in data collection and data analysis will be blinded to participants' group allocation throughout the entire trial.

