### Outcome Measures

#### Primary Outcome Measure

##### Flow-Mediated Dilation

FMD is a non-invasive technique and the gold standard to measure endothelial function. The FMD measurement will be performed at the brachial artery, at the non-dominant side, following a standardized protocol described by Thijssen et al. (67). An ultrasound system (GE, Vivid 7) with a linear probe (12L, 7–10 MHz) will be used to assess the brachial artery diameter based upon longitudinal images with the lumen–intima interface visualized on both (anterior and posterior) walls. The arterial occlusion will be performed *via* a sphygmomanometer cuff (Hokanson, SC5™, 6 × 83 cm), placed 5–10 cm below the elbow, inflated and held between 220 and 240 mmHg (68, 69) for 5 min. For stability, the probe will be hold tight by a stand-off probe support. To assess the effect of the reactive hyperemia, the brachial artery will be visualized pre-occlusion for 90 s (mean of three individual clips comprising each 30 s) and post-occlusion for 4 min with additional 15 s before cuff release. Although it is recommended to perform an FMD measurement in fasting state (67), this is not feasible since the entire protocol lasts around 5 h. However, the measurements will be done 15 and 150 min after food intake (standardized breakfast at each visit). Boundaries for diameter measurement will be identified automatically by means of a boundary tracking software (Quipu, diastolic phase) and optically controlled by a single, independent and blinded investigator. When tracking is impaired, the investigator will restore this tracking with maintenance of region of interest. Data obtained from false tracking or altered region of interest will be removed from analysis. FMD measurement is a challenging technique and has a significant learning curve. At least 100 scans supervised by a specialist were done prior to the start of this study.

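### Staff blinding rests on two trial-wide capsule numbers, so any single disclosure decodes all 150 doses for those who see the labels, and Table 4 offers one route to such a disclosure

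*Protocol article*

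**What the plan says.** Under Blinding and Randomization, the article describes a cross-over in which "every participant will receive CF-enriched and placebo capsules". Participants pick a sealed envelope at the first study day, and "type of capsules will be indicated by number 1 or number 2". Participant blinding is attributed to the two capsule types looking and tasting the same. Staff blinding is attributed to the numbering: "since type of capsules will be identified by numbers, outcome assessors and personnel involved in data collection and data analysis will be blinded". The claim covers the full length of the study. The section mentions no participant-specific kit number and no change of code over time.

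Three other places bear on this:

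- **Study Protocol, Table 4.** It lists 8 capsules for the cocoa-flavanol (CF) dose and 6 for placebo. Its footnote says the amounts are for the total intake. The text after the table has the investigator check that all capsules are swallowed.
- **Flow-Mediated Dilation (primary outcome).** Diameter tracking is automatic, with visual control by one reader described as independent and blinded. That control involves judgement: "When tracking is impaired, the investigator will restore this tracking with maintenance of region of interest". Data from false tracking or a changed region of interest are removed.
- **Data-Analysis Plan.** Visit order stays in the model only if it is significant, and a list of covariates is to be considered.

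**The concern.** A code that hides treatment should limit what one leak can reveal. A number attached to the capsule type, and shared by every participant, is the treatment under another name. It protects the blind only until someone learns the content of one numbered dose. From then on, each record bearing a 1 or a 2 is readable, for past and future visits alike.

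This matters because several steps that affect the primary result leave room for choice: repairing tracking, discarding FMD data, and deciding which terms stay in the model. The direction of the expected effect is also stated in advance in the Introduction. A person who makes such choices while knowing the code could favour CF across the whole data set, not in one participant only.

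**Working it through.** **Inputs from the article**

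- Group sizes (Eligibility Criteria): 15 T2DM with hypertension, 10 T2DM without, 30 essential hypertension, 20 healthy. The drug subgroups agree: 3 × 5 = 15 and 3 × 10 = 30.
- Doses per participant: 2, one CF and one placebo.
- Distinct labels: 2.
- Capsules per dose (Table 4): 8 CF, 6 placebo.

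**Step 1. Number of doses sharing the labels.** The article gives the total only as four group sizes. 15 + 10 + 30 + 20 = 75 participants; 75 × 2 = 150 doses.

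**Step 2. What one known dose reveals.**

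| Coding | Doses decoded | Share |
|---|---|---|
| Two trial-wide numbers | 150 of 150 | 100% |
| Participant-specific codes | 2 of 150 | 2/150 = 1.3% |

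With participant-specific codes the second dose is decoded because the same person's other visit follows by exclusion. The 100% applies only to people who see the labels.

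**Step 3. Sensitivity to the chance of a leak.** The article gives no leak probability. For illustration, assume that each dose is disclosed independently with probability p. With two trial-wide numbers, the chance that everything is decoded is 1 − (1 − p)^150. With participant-specific codes, the expected share decoded is 1 − (1 − p)^2.

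| Assumed p | Full decoding, two numbers | Expected share, participant-specific |
|---|---|---|
| 0.1% | 13.9% | 0.2% |
| 0.5% | 52.9% | 1.0% |
| 1% | 77.9% | 2.0% |

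These rows show how the two schemes scale. They do not estimate what happened in this trial.

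**Step 4. Is there a disclosure route in the document?** The blinding section rests on capsules that look and taste alike and on the numbering. Table 4 gives different counts for the two doses (8 − 6 = 2 capsules), and a member of staff observes the intake. Taken together, a person who sees the number swallowed and knows Table 4 can tell which dose it is, and can then read the label on every other record. Identical capsules do not hide a difference in count. The article does not say how the two statements fit together.

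**Step 5. What recoding can and cannot cure.** Participant-specific codes stop knowledge gained at one dosing from spreading to other participants' records. They do not hide a visible difference in count from the person who watches each dose. The count therefore has to be resolved separately, and matching the counts would not by itself cure the shared label.

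**The case against.** The strongest reply is that two labels do not break a blind; only a disclosure does, and the article reports none. This stands. A reader might infer that the claim of blinding throughout the trial is false. The documents do not support that. They show a scheme with no containment and one plausible route to a leak.

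Three further limits also stand:

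- **The FMD reader.** A reader might infer that this person is unblinded once the code is known. The article calls the reader independent and blinded, says only that clips are stored as DICOM files on a central server, and does not say that the 1/2 label travels with them. A reader who never sees the label learns nothing from a leaked code.
- **The analyst.** A mixed model with supplementation terms needs a two-level treatment variable, and a masked two-code file is ordinary practice. Guessing the key from which code has the higher FMD is possible under any kit labelling, so kit codes do not cure it. The contrast of 150 against 2 does not carry over to the analysis file.
- **Other triggers.** Caffeine (23 against 24 mg) and theobromine (179 against 180 mg) are closely matched, so a recognisable response to a single dose is speculative.

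It can also be said that an article leaves key custody, file naming and code release to the full protocol. Their absence is indeed no finding. That reply does not reach the main point, because the article itself states the two-number label and offers it as the basis of staff blinding. Nor does it explain the capsule counts in Table 4.

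**Conclusion.** The point holds as a weakness in how the blind is built. Staff blinding depends on two numbers that serve all 75 participants, so one disclosure exposes 150 of 150 doses to everyone who sees the labels, against 2 of 150 with participant-specific codes. The difference in capsule count in Table 4, with intake observed, makes such a disclosure more than hypothetical and sits badly with the blinding section.

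This rests on two readings. The first is that 1 and 2 keep the same meaning for every participant, which is the natural sense of the text but is not stated outright. The second is that Table 4 describes the doses as actually handed over. The risk is clearest for staff present at dosing. It reaches the FMD reader only if the label does. No bias in FMD, in size or direction, can be computed from the document, and none is claimed.

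**What to change.** 1. Reconcile Table 4 with Blinding and Randomization: state whether the two doses differ in capsule count as given and, if so, how staff who see the intake and the participants remain blinded.
2. For the remaining doses, replace the 1/2 label with participant- and visit-specific kit codes. The list should be held by an existing person with no part in assessment or analysis.
3. Make sure FMD clips, including those already recorded, carry only a random per-visit ID when they are read.
4. Give the analyst a masked treatment code, and release its meaning only after FMD reading, exclusions and model choices are locked.

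The cost is a slightly more complex code list, some relabelling and renaming of files. No extra visits are needed. The benefit of step 2 is limited: measurements began in October 2018, the article appeared in March 2021 and the end was expected in June 2021, so relabelling helps only the visits still to come. Steps 3 and 4 can still protect completed visits wherever reading and analysis have not yet been done.

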#### Data Management

All researchers, outcome assessors, data collector, data manager, data entry personnel, and statistician will receive special training regarding the standard procedure and data management. During the recruitment period, our data collector will record the baseline characteristics of participants in case report forms and all data will be checked by the data manager.

Study data will be pseudonymized, collected, and managed using REDCap, a secure, GDPR-proofed, web-based software platform designed to support data capture for research studies, providing (1) an intuitive interface for validated data capture, (2) audit trails for tracking data manipulation and export procedures, (3) automated export procedures for seamless data downloads to common statistical packages, and (4) procedures for data integration and interoperability with external sources (64, 65).

Solely two main investigators (endocrinologist and study responsible) will have the authority to decode the pseudonymized data. Concerning obtained data of FMD measurements, all clips will be saved in dicom-format and stored at a central server (University Ghent).

#### Adverse Events and Safety Monitoring

Adverse events after intake will be described as it is monitored by oral interrogation during the study day and by e-mail if participants experience some side-effects. So far, no adverse effects were defined in literature. However, in the article of Monagas et al. (66) 1 out of 42 included subjects reported constipation during the intake of cocoa concomitant with 250 mL skim milk for 4 weeks, which was solved by increasing fiber intake.

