This acute, randomized, double-blinded, placebo-controlled cross-over study aims to investigate whether a single intake of a high dose of CF (790 mg flavanols) induces an improvement in endothelial function (primary outcome), a reduction in BP, and an enhancement in muscle vasoreactivity and oxygenation in patients with T2DM compared to healthy controls.

Because hypertension is a common comorbidity in patients with T2DM and as little is known so far concerning possible interferences between antihypertensive drugs and CF actions especially in patients with diabetes mellitus, this study will additionally investigate possible influence of beta-blockers (BB), angiotensin converting enzyme inhibitor (ACEi), or angiotensin receptor blocker (ARB) in diabetic persons with arterial hypertension and non-diabetic persons with essential hypertension treated with these drugs.

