#### Additional Outcome Measures

In each participant, physical activity [steps per day and moderate-to-vigorous physical activity (MVPA)] will be evaluated with an accelerometer [Actigraph wGT3X-BT, dominant side, hip (75)] and glycemic excursions (percentages of time in hyper- or hypoglycemic ranges and time in range), risk for hypo- and hyperglycemia (Low and High Blood Glucose Indexes, LBGI and HBGI), and glycemic variability [standard deviation, coefficient of variation, and mean amplitude of glucose excursion (MAGE)] (76) by continuous interstitial glucose measurement (blind mode, IPro2, Medtronic, abdomen) for 1 week, immediately after the second study day. During this week, the above-mentioned restrictions concerning food intake and physical activity are not applicable and participants are encouraged to maintain their normal daily habits. Additionally, participants are asked to fill in a diary concerning their food intake and their physical activities for each day.

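### Active adverse-event questioning is described only for the study days, so mild events that start after a participant leaves, especially after the second intake, may be under-counted

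*Protocol article*

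**What the plan says.** The section Adverse Events and Safety Monitoring gives two routes of collection: events are "monitored by oral interrogation during the study day and by e-mail if participants experience some side-effects". It says that events will be described. The only specific effect it names comes from an earlier study, in which "1 out of 42 included subjects reported constipation" "during the intake of cocoa concomitant with 250 mL skim milk for 4 weeks".

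Two other sections show when participants are in contact with the study after taking capsules. Study Setting and Organization separates the two test days: "A wash-out period of minimal 3 days and maximal 2 weeks is provided". Additional Outcome Measures places accelerometry and glucose monitoring "for 1 week, immediately after the second study day", with a daily diary on food and physical activity. Neither section mentions symptoms or adverse events.

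**The concern.** The two routes work differently. Oral questioning reaches everyone. E-mail reaches only those who notice a symptom, link it to the capsules and take the trouble to write. Mild complaints that begin in the evening or on the following days are the ones most likely to go unreported.

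The two intakes are also followed up differently. After the first, the participant returns 3 to 14 days later and is questioned again as part of the same protocol, so a late effect could come up then, although the text does not say that the interval is asked about. After the second, no further questioning is described.

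At stake is how the published description of adverse events can be read. If few or none are reported, a reader cannot tell good tolerance from silence. The Introduction says that the trial may serve as a sort of pilot for long-term trials, so later investigators may look at that description even though the remark itself is about efficacy.

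**Working it through.** **1. The plan's own figure.** The cited rate is 1/42 = 2.4%. Its exact (Clopper-Pearson) 95% interval runs from 0.06% (2.5% point of Beta(1, 42)) to 12.6% (97.5% point of Beta(2, 41)). The planned number is 15 + 10 + 30 + 20 = 75 (Eligibility Criteria).

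- At the cited rate unchanged, 75 × 1/42 = 1.8 expected cases, and the chance of at least one is 1 − (1 − 1/42)^75 = 84%.
- At one tenth of that rate (an assumption), there are 0.18 expected cases and a 16% chance of at least one.
- Across the interval, the expected count runs from 75 × 0.0006 = 0.05 to 75 × 0.1257 = 9.4.

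The cited case arose over 4 weeks of intake, while each participant here takes cocoa flavanols once. The figure says almost nothing about what a single dose should produce, so it cannot be used to test the monitoring.

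**2. Length of the active window.** Flow-Mediated Dilation gives the visit length: "this is not feasible since the entire protocol lasts around 5 h". Before the capsules come:

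- blood pressure, 3 + 21 = 24 min (Blood Pressure);
- breakfast, 15 min, and rest, 15 min (Study Protocol);
- the baseline dilation test, 1.5 + 5 + 4 = 10.5 min (Flow-Mediated Dilation).

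The sum is 24 + 15 + 15 + 10.5 = 64.5 min. At most 300 − 64.5 = 235.5 min, about 3.9 h, remain after intake. Study Protocol puts all post-intake measurements within 2 h, so the real window may be shorter. Against the 72 h of the shortest wash-out, 3.9/72 is about 5%. This is for scale only, since the wash-out is not a defined risk period for adverse events.

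**3. The two intakes side by side.**

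| | After intake 1 | After intake 2 |
|---|---|---|
| Same-day oral questioning | yes | yes |
| Later contact | second visit, day 3 to 14 | one week of devices and diary |
| Later oral questioning | yes, but not stated to cover the interval | none described |
| E-mail | if the participant writes | if the participant writes |

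**4. Size of the under-count.** If no event were recorded in 75 participants, the one-sided 95% upper bound would be 1 − 0.05^(1/75) = 3.9%, provided that every event was captured. Correcting this for missed events needs the share of late events that reach the study by e-mail. The documents do not give that share, and nothing in them narrows it between 0 and 1.

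**The case against.** The strongest reply is that this is a condensed article. Whether the second visit asks about the interval, what happens when devices are returned, and the reporting window may all stand in the full protocol. That weakens any complaint about missing detail. It does not remove the point, because the article does state a method for events outside the study day, and that method depends on the participant's initiative.

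Second, coverage is better than one questioning session. The second visit follows the same protocol and can pick up late effects of the first dose. Study-day questioning also spans the 90 to 120 min at which the article places peak flavanol concentrations. Both facts stand, and they narrow the gap mainly to the time after the second intake.

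Third, follow-up differs by period rather than by capsule, and order is randomised, so losses should fall about equally on cocoa and placebo. This largely stands. One reservation is that Table 4 lists 8 active and 6 placebo capsules, while Blinding and Randomization relies on identical look and taste. If participants notice the count, voluntary reporting could differ by capsule.

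Fourth, the article lists no safety objective and plans no formal safety comparison. That is correct, and it limits the consequence to how a descriptive statement is read.

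A reader might infer that the monitoring is blind to the one adverse effect that the protocol cites. The documents do not support this: constipation was seen during 4 weeks of intake with skim milk, and nothing suggests that it is an expected effect of one dose.

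**Conclusion.** The point holds as a modest one. As described, everyone is asked about adverse events only on the study days. Outside them, collection depends on e-mail from the participant, with the clearest gap after the second intake. Mild late events may therefore be under-counted.

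A reader might go further and conclude that late events are certainly under-counted, or attach a corrected upper bound to a zero count. Neither follows. Any such bound needs an assumed e-mail capture rate, and that rate would not apply to events elicited by questioning on the day. Nor do the documents support a claim that the comparison of cocoa with placebo is biased: randomised order makes lower counts the main effect, subject to the reservation about capsule numbers.

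No primary or secondary efficacy result is touched. The conclusion assumes that the article describes the collection method fully. If the full protocol already includes an interval question and a contact after the second intake, it is enough to say so.

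**What to change.** In Adverse Events and Safety Monitoring, add one open, non-leading question put to every participant at two points:

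- on arrival at the second visit, before the capsules, covering the time since the first visit;
- at the end of the device and diary week after the second visit, in person or, if devices are returned without staff contact, by a standard message to all.

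Record the onset date of each event. For the summary, count events in the same post-capsule window in both periods, no longer than the 3-day minimum wash-out, and tabulate them by capsule type. Keep e-mail as an extra route.

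The cost is a few minutes per participant and a case report form field, plus some additional trivial events. Recall intervals will still differ somewhat: 3 to 14 days after the first intake against about a week after the second. Timing is a further limit. The first measurement was in October 2018, the article appeared in March 2021 and the end was estimated for June 2021, so the change may reach only the remaining participants. The report should then state which collection method applied to whom and should not pool the two without comment.
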